## Abstract

**Background:**

Breast cancer is the leading cancer in women in France both in incidence and mortality. Organized breast cancer screening (OBCS) has been implemented nationwide since 2004, but the participation rate remains low (48%) and inequalities in participation have been reported. Facilities such as mobile mammography units could be effective to increase participation in OBCS and reduce inequalities, especially areas underserved in screening. Our main objective is to evaluate the impact of a mobile unit and to establish how it could be used to tackle territorial inequalities in OBCS participation.

**Methods:**

A collaborative project will be conducted as a randomized controlled cluster trial in 2022–2024 in remote areas of four French departments. Small geographic areas were constructed by clustering women eligible to OBCS, according to distance to the nearest radiology centre, until an expected sample of eligible women was attained, as determined by logistic and financial constraints. Intervention areas were then selected by randomization in parallel groups. The main intervention is to propose an appointment at the mobile unit in addition to current OBCS in these remote areas according to the principle of proportionate universalism. A few weeks before the intervention, OBCS will be promoted with a specific information campaign and corresponding tools, applying the principle of multilevel, intersectoral and community empowerment to tackle inequalities.

**Discussion:**

This randomized controlled trial will provide a high level of evidence in assessing the effects of mobile unit on participation and inequalities. Contextual factors impacting the intervention will be a key focus in this evaluation. Quantitative analyses will be complemented by qualitative analyses to investigate the causal mechanisms affecting the effectiveness of the intervention and to establish how the findings can be applied at national level.

**Trial registration:**

Registered on ClinicalTrials.gov, December 21, 2021: NCT05164874.

## Introduction

### Background

Cancer remains the leading cause of death and a pathology where health inequalities are particularly marked. These inequalities are evident at all stages of the medical history of the disease and are revealed with indicators such as incidence, survival and mortality. Regarding detectable cancers like breast cancer, screening is a key step in the construction of inequalities [1]. In most European Union member states, breast cancer screening is based on regular mammography screening with some differences in implementation [2]. In France, breast cancer is the leading cancer in women in incidence and mortality with 58,968 new cases estimated for 2017 and 11,883 deaths in the same year [3]. Mass screening has been organized nationwide since 2004 according to European recommendations, with high quality assurance. A screening mammography is offered every two years to women aged 50 to 74 with an average risk. Women are invited by management structures in charge of this screening (SMS) to visit an accredited radiologist’s office where radiological imaging of the breast (two views) and a clinical breast examination are performed. The radiologist interprets the images. If the images are normal, a second radiologist reviews them. In the last three years, the national participation rate in organized breast cancer screening (OBCS) has remained stable around 48% [Santé Publique France], while the rate of opportunistic screening with attendance is estimated at 15%. However, the European Union recommendation is 70% [4].

Few literature reviews on OBCS have been conducted to identify common determinants of non-adhesion to it, yet the organization of OBCS, its screening modalities and targeted populations (low income, ethnic group, rural areas) differ between countries [5, 6]. Consensually established determinants are usually grouped in five categories: (a) socio-demographics characteristics such as age, marital status, low income; (b) environmental characteristics like living in rural areas [7]; (c) health system utilization: having a general practitioner; (d) health behaviour such as performing other types of screening, alcohol or tobacco consumption and (e) psychological factors such as beliefs and concerns. Most of these factors are socially determined, and social inequalities in participation in OBCS are frequently reported. In France, participation rates vary greatly, some departments having a participation rate close to the European benchmark and others having a very low rate (< 25%). By using ecological indexes of deprivation [8] and small geographical units, social and territorial inequalities have been highlighted with a low participation for women living in deprived areas or far from a radiologist’s office [9–12].

*The World Health Organization* (WHO) considers social determinants to be the main causes of inequalities in health. These are the circumstances in which people are born, grow up, live, work and age and the systems set up to deal with disease. These determinants are multiple, ranging from individual to global, and they interact in complex ways. Determinants of non-adhesion to OBCS can also be established by using social ecological models that incorporate all the social and ecological factors that affect breast screening participation [13]. In summary, demographic, socio-economic determinants and health behaviours concern individuals, social support and social networks have an interpersonal dimension, and cultural norms and community organization involve issues pertaining to the community. Another dimension is the health care system, which involves factors such as health insurance, travelling distance to health facilities. Finally, there are structural factors relating to inequalities in wealth and place of residence. When modifiable, these determinants can be the target of interventions to increase OBCS participation and reduce inequalities in participation.

### Rationale

Various strategies can be implemented to increase participation in OBCS in deprived populations or in remote areas. Among these, mobile mammography units (MMUs) are currently operating in many areas in the world : USA [14], Brazil [15], and at least 7 countries in European Union [16]. Depending on the country, MMUs are included in the national program of organized cancer screening (Sweden [17], or in regional programs [10, 14, 18], in addition to the national screening program. MMUs are considered to increase access to OBCS for under-screened groups by increasing physical and economic access while reducing barriers for women like structural barriers and out-of-pocket costs. However, very few studies have provided robust evidence-based data through an RCT. Moreover, regardless of their target, most evaluations have not taken the existence of proven inequalities into account in their design and have not set out to reduce social and territorial inequalities in participation as an objective [19].

In France, a retrospective study conducted in 2019 in a rural area suggested that, when used in remote areas, MMUs can reduce social and territorial inequalities [10]. However, the potential value of MMUs depends on socio-demographic, geographical and medical characteristics. Therefore, there is very little evidence to help public health decision-makers in France to organize OBCS that aims to reduce health socio-territorial inequalities.

### Objectives and trial design

Only an experiment rigorously conducted and evaluated over a large territory would provide reliable information on the effectiveness of an MMU to increase participation and reduce social and territorial inequalities, with a view to a subsequent national rollout. We thus set up a prospective randomized controlled cluster trial in the general population with parallel group superiority trial and 1:1 allocation ratio for clusters to assess the gain in participation obtained with an MMU in remote areas in France. This population health intervention research is part of a collaborative project for MMU evaluation in reducing or even eliminating territorial inequalities in participation in OBCS in France. The secondary objective is to identify the most efficient modalities for incorporating an MMU in OBCS.

## Methods

### A multi-partner project

This project is collaborative, multi-partner and intersectoral. It involves several research teams, a screening management structure (SMS) (Centre Régional de Coordination des Dépistages des Cancers Normandie), institutional partners, local (departments) stakeholders and associations. It is managed by the U1086 INSERM research team (ANTICIPE), which is in charge of its design and evaluation. The SMS is in charge of organizing the OBCS (collecting data, consent, sending invitations, organization of second reading and managing follow-up). The four French departments where the intervention will take place (Eure, Calvados, Manche, and Seine-Maritime) have purchased the MMU collectively. During the 2 years of the intervention, the MMU will be made available free of charge to the SMS. The SMS oversees its maintenance and recruits the necessary staff (driver, secretary, radiographer and doctors). Doctors in the four departments are partners in the study and devote part of their working time to the MMU. The MMU itinerary is established in collaboration with a geography research team (IDEES UMR CNRS 6266) that will optimize the itinerary by integrating various logistic constraints such as distance and available parking space. Other research collaborations have been established with a social work institute (Institut Regional du Travail Social) to list all medical, social and associative resources that could be mobilized, such as networks of social workers, health centres, medico-social services and associations. These local stakeholders will inform the women about the OBCS and the MMU. Promotion Santé Normandie (health promotion institute) will ensure coordination and common understanding between the partners, and will develop new communication tools dedicated to OBCS in an MMU. The AAPRISS platform (Apprendre et Agir Pour Réduire les Inégalités Sociales de Santé), which is specialized in the social determinants of health and social inequalities in health, will be involved in developing the theoretic basis for the intervention.

The research is funded by the French National Cancer Institute (Institut National du Cancer) for 48 months, by the regional health agency (Agence régionale de Santé Normandie) in charge of OBCS in the region, and by a grant from the association ‘Ruban Rose’ (https://www.cancerdusein.org/).

### Study setting

This 2-year intervention will begin in March 2022 in the departments of Eure, Calvados, Manche, and Seine-Maritime (Normandy Region of France, except the Orne department, which already has an MMU). The territory covered is 23,791 km^2^ with just over 3 million inhabitants.

### Trial design

The design is a prospective randomized controlled cluster trial in the general population with parallel group superiority trial and 1:1 allocation ratio for clusters. The schedule of enrolment, intervention and assessment is shown in Table 1. This protocol is reported according to the recommendations of the Standard Protocol Items: Recommendations for Interventional Trials (SPIRIT).

**Table 1 Tab1:**
[figure not shown]
Schedule of enrolment, intervention, and assessment of mobile mammography unit (MMU) trial, following the Standard Protocol Items Recommended for Clinical Trials (SPIRIT) guidelines

### Eligibility criteria

Women invited to the MMU are all women whose last mammogram is more than 22 months old. Compared to the usual cycle of screening campaigns, these are the women invited at the moment when the MMU passes close to them as well as all the women who have not participated since their last invitation.

### Informed consent

In the invitation to screening, a legal notice informs women of the storage and use of their data for evaluation purposes and of their right to object to this use. This trial does not involve collecting biological specimens for storage.

### Intervention

It is now widely accepted that when implementing public health interventions aimed at reducing socio-territorial inequalities, some consensually recognized principles should be adopted. These include the existence of a social gradient across society, the relevance and the value of the principle of proportionate universalism [20] and the multilevel, intersectoral, multidisciplinary nature of the intervention [21]. These principles have been adopted in our program and research.

#### Intervention description: screening appointment

The main intervention consists in an offer of an appointment at the MMU in addition to the current OBCS. This complementary mode of screening offers women who live the furthest away from the radiologist’s office the possibility to undergo screening in the MMU. All women eligible for OBCS and living in the area selected for the intervention are invited by the SMS to participate either in a radiologist’s office or in the MMU. OBCS for women in the control group is not modified. The MMU is equipped with a latest-generation digital scenographer as well as an ultrasound system according to the current rules published by the National Institute of Cancer. The quality of the mammographic radiographic equipment is also certified by the Nuclear Safety Agency. Compliance with the specifications is ensured by the presence on board of the MMU of a radiographer and a doctor. The first reading will be made immediately if the doctor is a radiologist. If necessary, an enlargement, additional images or an ultrasound will be performed. This procedure currently represents between 15% and 20% of all mammographies performed. Otherwise, the first reading is differed and organized with a radiologist subsequently by the SMS. In both cases, when the first reading is negative, the second reading is carried out by another radiologist, as is currently the case.

#### Intervention description: preventive actions

About 2 weeks before the MMU is parked at the appointment site, the women concerned receive information about it. For most women, this is the first time they learn of the existence of the MMU.

The stakeholders provide various forms of information on OBSC and on the organization of screening in the MMU. A dedicated decision-making tool has been developed for this purpose. All those involved have been informed about the need to adhere to the protocol and the importance of respecting the intervention and control groups. Preventive actions are organized in collaboration with the research team and are targeted mainly on the women in the intervention group. However, in the areas where the intervention takes place, preventive actions undertaken prior to the MMU visit are organized by and under the responsibility of the stakeholders according to the territory they cover and their availability. In addition, a dedicated website https://mammobile-normandie.fr/ provides further downloadable information including a video of screening in the MMU and the times and days when it will be parked in their vicinity.

### Assignment of interventions

#### Definition of clusters

The cluster in this study is a group of IRIS (Ilots Regroupés pour l’Information Statistique), which is the smallest administrative unit in France for which census data are available and represents about 2000 inhabitants. Thanks to the geomatics tools of the MapinMed platform at U1086 INSERM (national platform officially labelled by the National League against Cancer), all the women in the target population for OBCS in Normandy are geolocated and geocoded (CNIL authorization N ° 921203). Thus, for each woman, history of screening, date of current screening invitation, IRIS of residence, level of social deprivation according to the European Deprivation Index (EDI) and the distance between the woman’s house and the nearest approved radiologist’s centre are extracted from the SMS database or calculated (EDI, distance). The EDI is an ecological deprivation index constructed according to Townsend’s concept of relative deprivation [8, 22]. It is calculated as the sum of weighted census variables. The 2011 French version of the EDI is computed for each IRIS as 0.32* % country birth + 0.36* % citizenship + 0.21* % tenure status + 0.32* % household size + 2.42* % no bath, no shower + 0.36* % marital status + 0.87* % education + 0.55* % professional activity + 0.80* % months unemployed + 0.70 * % occupation.

#### Sample size calculation

The U1086 INSERM research team has developed an algorithm in python v3.0 to constitute clusters combining some constraints in a regional scenario for the four departments. Eligible population data are available in the SMS screening database. First, it was estimated than the number of intervention days should not exceed 400 over 2 years (considering holidays, climatic and logistical hazards). Eight hundred days were considered to constitute a control arm. Based on the experience of the Department of Orne [10], it was estimated that around a hundred women had to be invited each day in order to perform around 30 mammograms daily. We also plan that, when possible, the MMU will park on the same site for at least two consecutive days so that women will have flexibility in attending. The population study (intervention arm and control arm) has been constituted to be as distant as possible from accredited radiology centres. After calculating the average travel time of women to the nearest radiology centre in each IRIS, 96,200 women were selected (algorithm stopped at the IRIS exceeding maximum population = 800 days of work*120 women = 96,000) in the 1131 most distant IRIS. To maximize aggregation of the IRIS according to travel time to the radiology centres, the most distant ones were selected and then merged with neighbouring IRIS, still by distance travelled, until areas of the expected population size were reached. This algorithm was applied to all IRIS according to distance rank until aggregation was no longer was possible. 91,982 women (95.6%) and 1067 IRIS (94.3%) were selected in the final population in 356 clusters (with 258 created by the algorithm). This algorithm allows geographical clusters to be constructed. The number of women is estimated on the basis of a previous screening campaign, so the real number will be known when the screening invitation has been sent. Table 2 shows the distribution of clusters between departments and arms. As it is a regional calculation according to the criterion of distance, the clusters are not equally distributed among the departments.

**Table 2 Tab2:** Clusters and distribution of women in each department

Department	Arm	Women number	*N* (%)	Cluster number	*N* (%)
Calvados	Control	14730	26875 (29.27%)	54	102 (27.64%)
	Intervention	12145		48	
Eure	Control	14036	27801 (30.27%)	58	111 (30.08%)
	Intervention	13765		53	
Manche	Control	8022	15630 (17.02%)	30	62 (16.80%)
	Intervention	7608		32	
Seine Maritime	Control	9919	21676 (23.60%)	43	94 (25.47%)
	Intervention	11757		51	
Total		91982		369^a^ (356)	

^a^13 clusters cover two departments

#### Allocation

Randomization in parallel was performed to constitute the intervention arm (*n* = 178 clusters) and the control arm (*n* = 178 clusters), corresponding to 45,275 targeted women in the intervention arm vs 46,707 in the control arm. Randomization was accomplished using a computer-generated random number. The information on the clusters and the intervention and control groups was then recorded in the database of the SMS. Patients, the data manager and the medical staff cannot be blinded regarding the intervention. The main characteristics of each arm are presented in Table 3. The mean travel time is 20.42 min in the intervention arm and 20.48 in the control arm. The higher the deprivation index score, the more the cluster is deprived.

**Table 3 Tab3:** Characteristics of intervention and control arms

	Intervention	Control
Clusters (*N*)	178	178
IRIS (*N*)	562	505
Women (*N*)	45275	46707
Travel time (min) mean [min-max]	20.42 [16.2;31.2]	20.48 [16.1; 30.1]
EDI mean [min-max]	− 0.77 [− 6,5 ;7.4]	− 0.87 [− 5.6 ;5.8]

Figure 1 represents the map of the four departments concerned by the intervention. Black contours represent the boundaries of the departments and grey contours represent those of the IRIS. The intervention areas are coloured pink and the controls grey. The dots represent the radiology office. The calculation includes the distance to the radiology office of the neighbouring departments.

**Fig. 1 Fig1:**
[figure not shown]
Trial geographic map

### Statistical method

The overall objectives of the study are to evaluate the intervention’s ability (a) to increase the participation rate in remote populations, (b) to reduce the socio-territorial inequalities of participation in OBCS in a regional area (Normandy) and (c) to understand how the intervention interacts with contextual factors and which causal mechanisms lead to these results in order to identify the optimal modalities for national rollout. The intervention will be analysed after 2 years.

#### Primary outcomes

Concerning the first two objectives, the main evaluation criterion will be participation in screening. Information on clusters, invitations and participation of women are available in the SMS screening database and recorded according to the quality criteria necessary for the monitoring and evaluation of screening. Participation will be measured and compared between the ‘intervention’ and ‘control’ arms, at aggregate level (cluster) and individual level in intent to treat. In both arms, a woman will be considered a non-participant 18 months after her last invitation. At the aggregate level, the comparison of screening participation will allow us to measure the raw and age-standardized increase in participation due to the intervention. At the individual level, multilevel logistic regressions based on cluster data will allow us to assess the increase in the probability of participating in screening after adjustment on social deprivation, age and other available individual characteristics. The analysis of all the screening data in the study departments, and in particular the comparison of remote (‘intervention’ or ‘control’) and nearby areas, will allow us to assess the impact of the intervention on reducing geographic inequalities in the Normandy region. Although the number of subjects in the study was calculated pragmatically, the intraclass correlation factor was estimated at 0.0083, which with an average area size of 318.6 women gives a design effect equal to 3.63. Therefore, the minimum significant difference in participation that we can prove will be 1.5%. Screening quality criteria will also be monitored using all the data available in the SMS database. Particular attention will be paid to the number of cases of lost to follow-up and delays in reading.

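### Neither of the two unranked comparisons names prior screening participation or department as a covariate; one primary analysis adjusted for both would gain precision and protect against chance imbalance at little cost

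*Protocol article*

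**What the plan says.** All references are to the Protocol article.

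- **Level of analysis (Primary outcomes).** The arms are compared "at aggregate level (cluster) and individual level in intent to treat". Neither level is ranked above the other.
- **Cluster level (Primary outcomes).** The comparison "will allow us to measure the raw and age-standardized increase in participation due to the intervention". No other adjustment is named.
- **Individual level (Primary outcomes).** Multilevel logistic regression is to estimate the gain in the probability of participating "after adjustment on social deprivation, age and other available individual characteristics". The last group of covariates is not listed.
- **Data held (Definition of clusters).** The items extracted or calculated include, "for each woman, history of screening, date of current screening invitation, IRIS of residence", as well as deprivation and distance to the nearest radiology centre.
- **Randomisation (Trial design; Allocation).** The design has a "1:1 allocation ratio for clusters". "Randomization was accomplished using a computer-generated random number", and no stratification or other restriction is described.
- **Size (Allocation; Table 2).** There are 178 clusters per arm, "corresponding to 45,275 targeted women in the intervention arm vs 46,707 in the control arm". Table 2 splits them over four departments and notes that 13 clusters cover two departments.

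**The concern.** Past participation is a natural candidate for the strongest predictor of future participation. The Eligibility criteria make it more relevant here, because they mix women who are just due for screening with women who did not respond to their last invitation. These groups can be expected to attend at different rates, and their mix can differ between clusters. Table 3 shows that the arms are close on travel time and deprivation, but gives nothing on past participation.

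Department was left to chance by the randomisation as described, and two departments came out with visibly different shares. Age-standardisation does not address that.

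Two things are at stake. Most of the variance inflation in this trial is between clusters, and cluster-level history is the obvious way to reduce it. And with two unranked comparisons and an open covariate list, the article leaves unclear which estimate will be set against the stated 1.5-point difference.

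**Working it through.** **1. The plan's own figures.** Primary outcomes gives an intraclass correlation of 0.0083 and a mean cluster size of 318.6.

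Design effect = 1 + (m − 1) × ICC = 1 + 317.6 × 0.0083 = 3.636, which agrees with the stated 3.63.

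The stated minimum difference of 1.5 points cannot be reproduced from the article, because alpha, sidedness, power and baseline participation are not given. Assuming 48% (the national rate in the Abstract), two-sided 5% and 80% power, it is 1.76 points with a design effect of 3.63.

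The totals in Table 2 give a smaller mean cluster: 91,982 / 356 = 258.4. The design effect is then 1 + 257.4 × 0.0083 = 3.136. I use 258.4 below and give 318.6 for comparison.

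**2. Where the variance lies.** Write the design effect as (1 − ICC) + m × ICC = 0.992 + 2.145 = 3.136. The between-cluster part is 2.145 / 3.136 = 68%.

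**3. Effect of adjustment.** Let Rw and Rb be the shares of within- and between-cluster variance explained by the covariates. The documents give neither, so these are assumptions.

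- Factor D = (1 − ICC)(1 − Rw) + m × ICC × (1 − Rb)
- SE = √[0.48 × 0.52 × (1/46,707 + 1/45,275) × D] = 0.3295 × √D points
- Detectable difference = (1.960 + 0.842) × SE

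| Rw | Rb | D (m = 258.4) | SE, points | Detectable difference | Power for 1.5 points | Detectable difference, m = 318.6 |
|---|---|---|---|---|---|---|
| 0 | 0 | 3.136 | 0.584 | 1.63 | 73% | 1.76 |
| 0.1 | 0.25 | 2.501 | 0.521 | 1.46 | 82% | 1.57 |
| 0.2 | 0.5 | 1.866 | 0.450 | 1.26 | 92% | 1.34 |

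The relative gain does not depend on alpha, power or baseline. √(2.501/3.136) = 0.89 and √(1.866/3.136) = 0.77, a reduction of 11% to 23%.

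**4. Department balance (Table 2).**

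| Department | Control | Intervention | Difference in share |
|---|---|---|---|
| Calvados | 14,730 / 46,707 = 31.5% | 12,145 / 45,275 = 26.8% | −4.7 |
| Eure | 14,036 / 46,707 = 30.1% | 13,765 / 45,275 = 30.4% | +0.4 |
| Manche | 8,022 / 46,707 = 17.2% | 7,608 / 45,275 = 16.8% | −0.4 |
| Seine-Maritime | 9,919 / 46,707 = 21.2% | 11,757 / 45,275 = 26.0% | +4.7 |

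Is this more than chance? The unit of randomisation is the cluster. A chi-square test on the cluster counts (54/48, 58/53, 30/32, 43/51) gives 1.32 on 3 df, p = 0.72. The counts sum to 369 because the 13 two-department clusters appear twice, so the test is approximate, but it is nowhere near a signal.

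How far could it move the raw difference? The largest shift is the sum of the positive share differences times the spread in participation between departments: (0.0035 + 0.0473) × 5 points = 0.25 points. For a 10-point spread it is 0.51 points. Both spreads are assumptions. Against the unadjusted SE of 0.584, 0.25 points is 0.43 SE.

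**The case against.** **A reader might infer that the trial's main comparison is unadjusted.** The article does not support this. The sentence after the cluster-level one sets out an adjusted individual-level model, and the two are not ranked. Its open wording on individual characteristics could well include screening history. It covers department and the cluster's earlier participation rate less clearly, since neither is an individual characteristic.

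**A reader might infer that the department imbalance biases the result.** It does not. Clusters were randomised, the imbalance is what chance ordinarily produces (p = 0.72), and a shift of 0.25 points is under half a standard error. Cluster-based inference already allows for it.

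**The Background does not show that these four departments differ.** Its remark about "some departments having a participation rate close to the European benchmark and others having a very low rate" describes France as a whole. No rate is given for Calvados or Seine-Maritime. A 10-point gap would be extreme. At 48% the between-cluster variance is 0.0083 × 0.2496, or about 20.7 squared points. With shares of 29.27% and 23.60%, a 10-point gap between these two departments would use at least 0.2927 × 0.2360 / 0.5287 × 100 = 13.1 of it, about 63%. This supposes that the ICC was estimated across these departments, which is not stated.

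**Covariate lists commonly sit in the analysis plan or the full protocol, neither of which is shown.** This stands as a limit. An unlisted covariate is not an error. What remains is that the article does fix the cluster-level comparison as raw and age-standardised, and a better choice is available from data already held.

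**The adjustment is not quite free.** Women newly reaching screening age have no previous round, 13 clusters need a department, and history needs a common cut-off date. These are real but small costs.

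**Conclusion.** The point holds as a recommended improvement, not as the correction of an error. The article leaves two comparisons unranked and names neither prior participation nor department in either, although screening history is held for each woman and no stratification is stated.

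Under the assumptions above (48% participation, two-sided 5%, 80% power, 258.4 women per cluster), adjustment would bring the detectable difference from about 1.63 points to roughly 1.46–1.26. On those assumptions the unadjusted comparison falls short of the stated 1.5 points and a modestly adjusted one reaches it. The direction of the gain is secure. Its size rests on the assumed shares of variance explained, which the trial team can estimate from earlier campaigns.

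The department imbalance is a secondary reason: at most about 0.25 points per 5-point spread, due to chance and removable by adjustment.

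**What to change.** In Primary outcomes, or in the analysis plan if it is still open:

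1. Name one primary analysis and specify all its covariates as baseline variables.
2. Adjust for department and the cluster's participation rate in the previous campaign. In an individual-level model, also adjust for the woman's previous-round participation (with a category for no previous round), age, deprivation index and travel time. In a cluster-level analysis, use regression on the cluster-level covariates.
3. Freeze screening history in both arms at one date before the first invitations, which Trial status gives as 18 February 2022.
4. Assign each of the 13 two-department clusters by a fixed rule, for example to the department holding most of its women.
5. Report a marginal risk difference. The plan states its detectable difference in percentage points, and a conditional odds ratio changes with the covariates in the model.
6. Keep the raw and age-standardised differences as supportive results.

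The cost is analysis wording, a dated extract of history and two coding rules. Screening history, area of residence, deprivation and distance are already extracted or calculated for each woman, so no new data collection is needed and the randomisation is untouched.
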